#### Instruments and measures

At baseline, we will collect socio-demographic data and indicators of health status for customers (e.g., age, gender, self-reported health history, education level, socioeconomic status, and household composition), and acculturation (DC metro area only). We will also collect characteristics of restaurants at baseline (e.g., ethnicity of owner, cuisine served). See Table 3.

**Table 3 tab3:** Overview of FRESH measures.

Tool used	Outcome	Time frame	Brief description
Primary	Customer dietary quality	Baseline, post-treatment	Regular customer diet quality in the last 30 days will be assessed using the ASA24-Hour Dietary Assessment Tool (ASA24). Healthy Eating Index (HEI) 2015 Score and individual component scores will be calculated from the ASA24 according to the HEI-2015 guidelines to assess changes in overall diet quality and changes within each component.
Secondary	Customer psychosocial constructs	Baseline, post-treatment	Psychosocial outcomes will be measured with scales that have been specifically developed and tested by our study teams, including knowledge, self-efficacy, and behavioral intentions around making healthy choices at restaurants. All scales have acceptable reliability and construct alpha’s (0.63–0.88).
Secondary	Customer restaurant food purchasing behaviors	Baseline, post-treatment	A food purchasing score will be calculated based on the frequency of visiting and ordering foods at participating restaurants in the past 7 days. Emphasis will be placed on documenting purchase of FRESH introduced and promoted beverages, side dishes and entrees.
Secondary	Customer socio-demographics	Baseline	We will collect data on customer age, sex, health history, education, socioeconomic status, household composition, and amount of time living in the United States.
Secondary	Customer skin carotenoid levels	Baseline, post-treatment	Regular customer skin carotenoid levels will be measured using the Veggie Meter®. Three readings will be taken at each data collection point, and the average across the three readings will be calculated and used to assess change from baseline to post-treatment, as an indicator of fruit and vegetable intake.
Secondary	Customer anthropometrics: height, weight, blood pressure	Baseline, post-treatment	Client body weight to the nearest 0.1 lb. will be measured using the Tanita-BIA (Model BF679W). Height to the nearest 0.125 inch will be measured with a stadiometer (Seca 213). Three measures will be made, and the closest two measures averaged. Blood pressure will be measured using the iHealth upper arm cuff (UPC 856362005005).
Secondary	Household food security and food assistance participation	Baseline, post-treatment	We will collect household food security using the 18 question USDA scale, and participation by household members in federal food assistance programs (WIC, SNAP, etc.).
Secondary	Customer exposure to FRESH intervention	Post-treatment	During post-intervention, we will assess exposure by using a standardized form, showing respondents representative materials from each component/phase of the intervention (e.g., posters, flyers, menus) and ask if he/she has seen/heard the material or participated in the activity (e.g., taste test), # times visited participating restaurants, etc. These measures will be recorded in the customer exposure questionnaire. See Supplementary Appendix 2.
Secondary	Restaurant characteristics	Baseline	Restaurant hours, average number of customers, cuisine served, primary spoken language of customers and staff, menu type, beverage availability, age of restaurant, cooking methods used, social media information, number of suppliers, frequency of food procurement/week.
Secondary	Restaurant sales impact	Baseline, post-treatment	We will collect the sales of promoted FRESH foods and beverages of the last week via recall, 9 times during the intervention.

#### Customer-level impact

The primary outcome of dietary quality will be assessed via reported dietary intake from the past 24 h using the ASA24-Hour Dietary Assessment Tool (ASA24). Customers will complete the ASA24 twice at pre-intervention, two weeks apart and this protocol will occur again at post-intervention. The overall HEI score will be calculated according to the methods outlined by the National Cancer Institute (42). All impact measures will be assessed pre-and post-intervention to calculate a change score.

Secondary outcomes at the customer level will be assessed by the Veggie Meter®. This instrument noninvasively measures carotenoid status using a laser for blue light excitation of carotenoids in the skin (43) and has proven validity (44–46). Anthropometric measures will include body weight to the nearest 0.1 kg measured using the Tanita DC-13C scale and height measured to the nearest 1 mm using a stadiometer. Percent body fat will be measured using bioelectrical impedance (Tanita-BIA Model BF679W). Psychosocial constructs will focus on how to make healthy food choices in restaurant settings. *Self-efficacy* will assess the confidence that the respondent feels to perform restaurant-related healthy behaviors. *Intentions* will assess respondents’ intention to perform specified restaurant-related healthy behaviors. Customer Exposure to components of the intervention (dose received) will vary among respondents based on measures such as their use of community media and how frequently they eat at participating restaurants. At post-intervention, we will assess exposure using a standardized form and show representative materials from each component/phase of the intervention and then ask respondents if he/she has seen/heard the material or participated in the activity (47).

#### Restaurant owner/manager impact instruments

General Restaurant Information including restaurant hours, social media usage, age of the restaurant, and staffing information will be collected via short questionnaire from the restaurant owners. The Restaurant environment—Observations of food service style, menu format, as well as menu labeling, amongst other items, will be collected at baseline and post-intervention. Restaurant owners’ psychosocial impact will be measured through self-efficacy and intention questions related to food and carryout operations.

#### Restaurant tracking form

Collected nine times throughout the intervention, restaurant owners will be asked to recall the restaurant ordering of foods that are culturally-relevant and most likely to be ordered as part of the FRESH-approved meals from the last 7 days. Data collectors will ask restaurant owners to recall the restaurant sales of the promoted foods and beverages sold in the last week. They will also report on the number still in stock and the amount of each item that was wasted, as well as perceived customer demand for promoted items.

### Sample size and power

Our power calculations are based on the primary hypothesis, which involves testing the change in mean Healthy Eating Index (HEI) of customers between study groups. Our chosen effect measure is the standardized mean effect of the intervention, representing the difference in mean change in HEI score between the intervention and comparison groups. This measure is standardized by the total variability in the outcome, denoted as the standardized main effect (ES).

$$\begin{array}{l} \mathrm{The standardized main effect}\;\left(ES\right)\\ \;=\frac{\mu_{I}-\mu_{C}}{\sqrt{\tau_{\mathrm{restaurent}}+\tau_{\mathrm{neighborhoods}}+\sigma^{2}}} \end{array}$$

Here, μ_I-μ_C is the mean difference of intervention and comparison groups, respectively. *σ*^2 corresponds to within cluster variation, τ_restaurant corresponds to between restaurant variation within neighborhoods, and τ_neighborhoods corresponds to between neighborhood variation within a site. For our calculations, we assumed a difference in means of 5 points in HEI score would be meaningful, leading to μI − μC = 5. Using data from one of our prior multilevel intervention studies (48), we estimated the standard deviation of the change in HEI outcome to be 9–10 points, giving us σ^^2^ = 9.52^^2^ ≈ 90. We also assumed the variance of change in HEI score between restaurants within a neighborhood, and between neighborhoods within a site, would be small relative to the variance within a restaurant, therefore assuming τ_restaurant = τ_neighborhood≈5_._ Thus, we aimed to be powered to detect an effect size of ES = 0.5. This is equivalent to detecting a medium-sized effect.

Power calculations were conducted using the Optimal Design program (49) and following the documentation for “Multisite cluster randomized trials with treatment at level 3 randomization” section. For all calculations, we assumed a significance level of *α* = 0.05, an effect size of *δ* = 0.5, a total of L = 2 sites (for Baltimore and DC metro area), and an effect size variability of 0, corresponding to fixed effects by site rather than random effects by site.

We varied the number of neighborhoods per site (*K* = 4 to 12), the number of restaurants per neighborhood (*J* = 2,3,4), and the number of customers per restaurant (*n* = 10 to 20). We varied the proportion of variability in the outcome explained by site (Baltimore vs. DC metro area) from 0 to 20% (*B* = 0, 0.1, 0.2). We varied the intra-class correlation coefficients for both the level 2 variable (restaurants) and the level 3 variable (neighborhoods) from 0.01 to 0.1 (ρπ = ρβ = 0.01, 0.05, 0.1). Finally, we assumed a loss to follow-up of 20%. Power is calculated as a function of the number of neighborhoods per site, the number of restaurants per neighborhood, and the number of participating customers per restaurant at initial and follow-up visits. If 8 neighborhoods are randomly assigned to intervention and comparison groups at each site (8 neighborhoods per arm total), the power to detect an effect size a difference of 5 HEI points will exceed 80% if we recruit at least 12 customers per restaurant (*N* = 576) when ICC = 0.05. These calculations account for a potential 20% loss to follow-up.

### Data analysis

The data analysis plan includes a visual review of completed surveys, data entry, data cleaning, exploratory data analysis using sociodemographics, acculturation, baseline health status variables, and multivariable analysis. The statistical plan is to: (1) examine intervention effects via calculating the change variable by subtracting the pretest score/intake from post-test score/intake (exploratory analysis), and then (2) conduct linear mixed-effect models for confirmatory testing of intervention effects across the two study groups.

Exploratory analysis will provide an assessment of the distributions of the outcomes, as well as reveal patterns of missingness and the need for additional data review and quality assurance. If any variable in the final dataset contains more than 5% missing values, we have prepared an imputation plan. To compare the intervention and comparison groups, our primary analysis will use a linear mixed effects model with an individual’s change in HEI score (post-intervention to pre-intervention) as the outcome variable, and including fixed effects for intervention and site, and random effects for restaurant and neighborhood. We will evaluate the effect of the intervention using a hypothesis test on the coefficient of the intervention group variable, which we will interpret as the difference in mean change in HEI score between treatment groups. We will also consider a fixed effect for an intervention-by-site interaction as a secondary analysis to see if the effect of the intervention is different by site (Baltimore vs. DC metro area). Finally, we will consider adjusting these mixed effect models to include customer-level (e.g., age, gender), restaurant-level (e.g., supplier impact questionnaire), and neighborhood-level (e.g., income, restaurant density) covariates.

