#### Randomization of restaurants

Following completion of the baseline data collection, the 16 census tract clusters will be randomized to intervention or comparison, using a public community-engaged approach we have previously employed in a Native American community setting (34). Half of the restaurants (*n* = 24) will therefore receive the FRESH intervention. At the customer level, half of the customer sample (*n* = 288) will be regular consumers at restaurants receiving the FRESH intervention. The sampling design is presented in Figure 3.

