#### Phase 3 (healthy meals)

This phase will emphasize the restaurant offering three new healthier meal options, that optimize dietary quality and taste following the DGA (35). A healthier meal is defined as 1 lean protein; AND 1 non-starchy vegetable; AND 1 vegetable (starchy or non-starchy) OR Fruit OR whole grain OR legumes. All components must be non-fried. As with beverages, entrees meeting FRESH criteria should be priced at or below the cost of comparable items. Existing menu items may be modified to meet FRESH criteria by simply adding a new side dish to an existing entrée. Specifically, a restaurant might already sell baked chicken that comes with two side dishes. If the restaurant already offers one side dish meeting FRESH criteria (e.g., collard greens), then the restaurant could develop one additional side dish, such as black-eyed peas, and create a menu item consisting of baked chicken, collard greens, and black-eyed peas to meet FRESH criteria. Digital and print media will be used to promote the three new healthy meals identified in Phase 1 to restaurant customers. Intervention restaurants will receive incentives in the form of supplier credit ($1,500/restaurant) to help offset the risk of providing these meals during the promotional period. This incentive will be received after the three new meals have begun to be sold by the restaurant.

In addition to supplier incentives described above, FRESH intervention staff will support restaurant owners/managers in sourcing the appropriate ingredients for proper FRESH implementation and will work directly with restaurant suppliers to allow them to anticipate stocking needs, a strategy we have used successfully in the past (36, 37). Lists of targeted meal ingredients will be provided to suppliers to ensure there are sufficient stocks.

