#### Impact assessment

Our primary study hypothesis is that regular customers of participating restaurants in FRESH intervention neighborhoods will demonstrate at least a five-point increase in dietary quality as assessed by the Healthy Eating Index 2015 (HEI) score, compared to restaurant customers living in FRESH comparison neighborhoods. We will assess this primary outcome in our consumer sample, as well as a variety of additional secondary outcome measures at the consumer, restaurant and supplier levels. All recruitment materials, consent forms and data collection instruments will be in English and Spanish. The language used will depend on the preferences of the respondent.

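### The primary HEI model leaves out baseline HEI, which gives up precision the trial could have at no cost; the planned change-score test is nonetheless valid

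*Protocol article*

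**What the plan says.** The Data analysis section of the protocol article states the primary model outright. It is a linear mixed model with individual HEI change "as the outcome variable, and including fixed effects for intervention and site, and random effects for restaurant and neighborhood". The intervention coefficient is the one tested, "which we will interpret as the difference in mean change in HEI score between treatment groups". An intervention-by-site interaction is secondary.

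The section then says that adjusted versions will be considered. Its examples are age and gender for customers, followed by "restaurant-level (e.g., supplier impact questionnaire), and neighborhood-level (e.g., income, restaurant density) covariates". Baseline HEI is not named.

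Two other places matter:

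- **Timing of baseline.** Randomization of restaurants says: "Following completion of the baseline data collection, the 16 census tract clusters will be randomized to intervention or comparison". Baseline HEI is therefore a pre-randomization variable.
- **Role of suppliers.** Impact assessment announces "a variety of additional secondary outcome measures at the consumer, restaurant and supplier levels". Under Phase 3, the intervention staff "will work directly with restaurant suppliers to allow them to anticipate stocking needs". Supplier credit and stocking lists are also part of the intervention.

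**The concern.** A change score fixes the coefficient of baseline at exactly 1. HEI here comes from two 24-hour recalls per time point, so it is noisy and customers with extreme baseline values will tend to move back toward the mean. The best coefficient is then below 1, and subtracting the whole baseline adds noise that a fitted coefficient would leave out. With 8 neighborhoods per arm, a chance difference in baseline HEI passes into the estimate with opposite sign.

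What is at stake is precision. The design clears its 80% target by only a few points, and a variable already collected could widen that margin.

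A smaller point concerns the optional covariates. The supplier questionnaire is given as an example without saying which time point would be used. Because the intervention acts on suppliers, a follow-up value could lie on the causal path to diet quality.

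**Working it through.** **Inputs from Sample size and power and the Discussion**

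- Difference to detect: 5 HEI points.
- Variance of change: 90 within restaurants, 5 between restaurants, 5 between neighborhoods. The total is 100, so the SD is 10, ES = 0.5 and the ICC is 0.05 at both levels.
- 16 neighborhoods (8 per arm), 3 restaurants each, 12 customers per restaurant. With 20% loss, 9.6 complete.
- α = 0.05, taken as two-sided (the sidedness is not stated).

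**Assumptions not in the document**

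- Pre-post correlation r of HEI between 0.3 and 0.7.
- Equal pre and post variances.

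**Step 1: reproduce the stated power**

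v = 0.05 + 0.05/3 + 0.90/(3 × 9.6) = 0.0500 + 0.0167 + 0.0313 = 0.0979.

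SE = √(4 × 100 × v / 16) = √2.448 = 1.565 points.

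The noncentrality is 5/1.565 = 3.20. A noncentral t with 2 × (8 − 2) = 12 df gives power of 83.4%. If site explains 20% of the variability, the highest value the protocol considers, power is 87.1%. The claim of more than 80% is reproduced.

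**Step 2: effect of adding baseline HEI**

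With a common variance V at both times, the variance of change is 2V(1−r). The variance after baseline adjustment is V(1−r²). The ratio is (1+r)/2.

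Two cases bracket the effect. In the cautious case, the ratio applies only to the 0.0313 within-restaurant term of v. In the favorable case, it applies to all three terms, which also requires the same correlation at restaurant and neighborhood level.

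| r (assumed) | Variance ratio | SE, within only | Power, within only | SE, all components | Power, all components |
|---|---|---|---|---|---|
| Planned model | 1 | 1.565 | 83.4% | 1.565 | 83.4% |
| 0.3 | 0.65 | 1.475 | 87.5% | 1.261 | 95.3% |
| 0.5 | 0.75 | 1.501 | 86.3% | 1.355 | 92.2% |
| 0.7 | 0.85 | 1.527 | 85.2% | 1.442 | 88.8% |

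If one df is charged for the covariate (11 instead of 12), the within-only powers are 86.9%, 85.8% and 84.6%, still above the planned model.

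**Step 3: chance baseline imbalance**

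Take r = 0.5 and the same ICCs for baseline HEI. Then V = 100/(2 × 0.5) = 100, and the baseline difference between arms has an SD of 1.565 points. A 1-SD gap shifts the change-score estimate by (1 − 0.5) × 1.565 = 0.78 points.

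This is not additional to Step 2. The two variances differ by 2V(1−r) − V(1−r²) = V(1−r)². In numbers, 1.565² − 1.355² = 0.61, and 0.78² = 0.61. The imbalance shift is exactly the precision lost in the all-components case and is already inside the planned SE of 1.565.

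**Step 4: bias over randomizations**

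In a simulation of 1,500 trials per scenario (16 neighborhoods, 3 restaurants, 10 customers, true effect 5), both analyses averaged about 5.0. The SDs of the estimates were 1.55 (change) and 1.27 (adjusted) at r = 0.3, and 1.57 and 1.37 at r = 0.5. The models differ in spread and not in center.

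**Step 5: supplier covariate**

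The same simulation adjusted for a post-intervention supplier score assumed to carry 20% or 50% of the effect. The estimate fell from 5.0 to about 3.9 or 2.5. This illustrates what a follow-up value could do; the protocol does not say that one would be used.

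**The case against.** The strongest defense is that nothing here is wrong or inconsistent. Sample size and power works with the difference in mean change and the SD of change, and Data analysis tests that same quantity with matching site effects and random effects. A change-score model is a legitimate analysis of a randomized trial, and it delivers the power claimed. All of this stands, so the point is an improvement and not the correction of an error.

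The size of the gain also rests on a correlation that the protocol does not give. The 89–95% range further needs that correlation to hold at cluster level. The cautious gain is about 2 to 4 percentage points. That stands too, which is why both cases are shown.

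A reader might infer that the primary estimate is biased, or that imbalance is a second harm beside lost precision. Steps 3 and 4 show neither: imbalance matters conditionally, in the one allocation drawn, and the planned SE already accounts for it.

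A reader might also infer that the supplier adjustment will bias the result. The text does not support this. Adjusted models are only to be considered, and they lie outside the primary model. The covariates are examples, so baseline HEI is not excluded. The other examples are background characteristics. Table 3 lists no supplier measure, and the questionnaire's timing is not described. The statement "All impact measures will be assessed pre-and post-intervention to calculate a change score" sits under Customer-level impact. A pre-randomization supplier value would do no harm.

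What the defense does not answer is that the primary model is spelled out, baseline HEI is available before randomization, and omitting it brings no benefit.

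**Conclusion.** The point holds as one of efficiency and should be acted on. The planned test is valid, unbiased over randomizations and meets its stated power. Adding baseline HEI would cut the variance to 65–85% of its planned value under equal pre and post variances, an assumed r of 0.3 to 0.7, and the same correlation at every level. Power would go from about 83% to 89–95%. If only within-restaurant variance shrinks, it would reach 85–88%. In the first case the dependence on chance baseline imbalance goes as well, as part of the same gain; in the second it goes only in part.

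The supplier covariate is a minor matter of stating the time point. It could mislead only if a follow-up or change value entered an optional adjusted model.

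**What to change.** In Data analysis, add baseline HEI to the prespecified fixed effects of the primary model, alongside intervention and site, and keep the random effects for restaurant and neighborhood. Either change or post-intervention HEI can be the outcome: once baseline is in the model the intervention coefficient is the same, and it can still be read as a baseline-adjusted difference in mean change.

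Add one clause limiting any further covariates, including the supplier impact questionnaire, to values measured before randomization.

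The cost is a sentence or two in the analysis plan, settled before outcome data are seen. No new data are needed, and the sample size statement can stay as it is.

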#### Economic data analyses

We will compare weekly unit sales before and after the implementation using a difference-in-difference approach between intervention and comparison groups and implement an Interrupted Time Series Analysis to explore if changes in the trajectory of sales after the introduction of FRESH can be attributed to the implementation of the program (50). Additional analyses will include sales of promoted foods and ratio of healthy-to-unhealthy food in intervention restaurants.

